### Sample size

Table 2 shows the sample size calculation for success rates ranging from 95% to 97%, alpha equal to 5%, with 90% power and an equivalence margin between the study groups of 10%. This table illustrates that the effective sample size of 81 teeth per treatment group will provide a power of 90% to assess effectiveness equivalence between the treatment groups. These rates were based on the systematic review of Innes et al. [3]. This calculation was based on the formula (Z _0.95_ + Z _0.90_)^2^ [Ps (1 – Ps) + Pn (1 – Pn)] / (Ps – Pn – D)^2^ (see http://people.ucalgary.ca/~patten/blackwelder.html) [14].

**Table 2 Tab2:** Sample size calculation

Rate	Teeth	Total required
80	274	548
85	218	438
90	154	308
95	81	162
97	49	98

Note: Rate of the outcome for the study groups, power = 90%, alpha = 5%, equivalence margin = 10%

Additionally, when we consider a hazard ratio (HR) = 1, moderate intraclass correlation (ICC) = 0.05, the percentage of teeth in each study group of 50%, the probability of observing an event of 90%, and two one-sided test (TOST) Zα = 1.64, this sample size of 81 teeth provides 80% power to test the equivalence between the study groups for margins ranging from 0.7 to 0.9. This sample size was calculated as described in [15].

Furthermore, assuming a dropout around 20%, the total sample size necessary will be 101 children. This dropout value was based on the experience of the research team from previous RCTs conducted in France [16]. This sample size is higher than those of past RCTs assessing the effectiveness of esthetic PPCs, which included 11 to 60 teeth per treatment group [6, 7].

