### Statistical analysis

The demographic and clinical characteristics of the participants (center, gender, age, Venham score 0–2/3–5, vigilant state/conscious sedation) and tooth pair (maxillary/mandibular molar pair, carious lesion/hypoplastic defect, two or more surfaces affected, with or without pulpotomy) will be described using mean and standard deviation (SD) for quantitative variables and percentages for qualitative variables.

Furthermore, bivariate analysis will be used to compare the baseline characteristics between groups (e.g., left/right molars, presence or absence of a restoration with a dental material on the antagonist tooth).

An intent-to-treat (ITT) analysis will be conducted. To assess the equivalent effectiveness of ZCs, we will use a multivariable Cox hazards regression model with shared frailty including success as the dependent variable (primary outcome defined by the absence of major failure: no = 0, yes = 1), and the treatment group variable as an independent variable. This analysis will also include the potential confounders age, gender, type of tooth (i.e., first or second primary molar), pulpotomy, number of surfaces affected by the lesion, and presence or absence of a restoration with a dental material of the antagonist tooth. Cox proportional hazards models, using the PHREG procedure will estimate the HR and the 95% CI. In these analyses, a random statement will be included identifying the variable “subject” as the variable that represents the clusters.

Secondary analysis will be performed to compare: the secondary outcomes of retention and fracture of PPCs; PI, GI, and DI on the crowned tooth and the two adjacent teeth; presence or absence of a restoration with a dental material of the antagonist tooth; and wear of the antagonist tooth between treatment (ZC) and control (SSC) groups.

Both the ITT and secondary analyses will be performed within a 2-year period at 6, 12, 18, and 24 months. Repeated measures analysis (mixed model approaches) will be performed, and the principal independent variables will be treatment and time. The alpha level will be equal to 5%. All analyses will be performed with SAS (version 9.4; Cary, NC, USA).

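### The trial is sized on a 10-point margin in success, but its primary analysis gives a hazard ratio with no single pre-specified equivalence margin, and the HR margins mentioned do not match 10 points

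*Protocol article*

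**What the plan says.** All references are to the protocol article.

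- **Objectives and hypotheses.** The working hypothesis is that success rates with zirconia crowns (ZC) and stainless steel crowns (SSC) are equivalent. Success means absence of major failure, and follow-up is 2 years.
- **Sample size, main calculation.** The inputs are "alpha equal to 5%, with 90% power and an equivalence margin between the study groups of 10" percent. The section concludes that "the effective sample size of 81 teeth per treatment group will provide a power of 90% to assess effectiveness equivalence between the treatment groups".
- **Sample size, supplementary calculation.** A second power statement assumes HR = 1, an ICC of 0.05, a 90% probability of observing an event and a two one-sided test (TOST) with Z = 1.64. It claims 80% power "for margins ranging from 0.7 to 0.9".
- **Statistical analysis.** Equivalence is to be assessed with a multivariable Cox model with shared frailty, adjusted for six covariates: "Cox proportional hazards models, using the PHREG procedure will estimate the HR and the 95% CI". No margin, rule comparing the interval with a margin, or estimate of the difference in success is attached to this analysis. The section adds: "Both the ITT and secondary analyses will be performed within a 2-year period at 6, 12, 18, and 24 months".

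**The concern.** An equivalence conclusion needs an estimate, an interval and a margin on the same scale. Here the hypothesis and the sample size are on the scale of success proportions, and the analysis is on the hazard-ratio scale. The one sentence that places margins on the HR scale gives a range, leaves its scale unclear, and rests on an event probability that does not fit the assumed success rate.

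The choice of scale affects the conclusion. Major failures are expected to be rare. A difference between two proportions near 95% is then estimated fairly precisely, but a ratio of two rare hazards is not. The same data could lie well inside ±10 points and still leave an HR interval far too wide for any equivalence claim. As written, the article does not say which HR interval would establish equivalence.

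**Working it through.** **Inputs from the article.** Success 95% in both groups (the Table 2 row that gives 81); margin 10 points; Z0.95 = 1.645 and Z0.90 = 1.282; 81 teeth per group, 162 in all; for the HR statement, HR = 1, ICC 0.05, event probability 90%, Z = 1.64, margins 0.7 to 0.9.

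**Assumptions made here.** Proportional hazards; independence of the two teeth of a pair when computing standard errors; for the HR power statement, a design effect of 1 + 0.05, because the cited method is not shown.

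**1. Main sample size.** (1.645 + 1.282)² × 2 × 0.95 × 0.05 / 0.10² = 81.4. The stated 81 reproduces.

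**2. The 10-point margin as an HR.** 85% against 95% success gives ln(0.85)/ln(0.95) = 3.17. At 97% success it is ln(0.87)/ln(0.97) = 4.57. The opposite bound has no HR counterpart, because 95% plus 10 points exceeds 100%.

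**3. The range 0.7 to 0.9 in points of success.**

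| Reading | Upper HR bound | ZC success at the bound | Points below 95% |
|---|---|---|---|
| HR 0.7 | 1/0.7 = 1.43 | 0.95^1.43 = 92.9% | 2.1 |
| HR 0.9 | 1/0.9 = 1.11 | 0.95^1.11 = 94.5% | 0.5 |
| log-HR 0.7 | e^0.7 = 2.01 | 0.95^2.01 = 90.2% | 4.8 |
| log-HR 0.9 | e^0.9 = 2.46 | 0.95^2.46 = 88.1% | 6.9 |

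Neither reading gives 10 points.

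**4. Does the stated 80% power reproduce?** Power = 2Φ(√d/2 × |log margin| − 1.64) − 1, with d the effective events.

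- Margins read as HRs, 162 teeth: d = 162 × 0.90/1.05 = 138.9. Power is 36% at 0.7 and 0% at 0.8 and 0.9.
- Margins read as log-HRs, 81 teeth in total: d = 81 × 0.90/1.05 = 69.4. Power is 79.8% at 0.7 and 96.5% at 0.9.

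Of the readings tried, 80% is reproduced only with a log-HR margin of 0.7 and 81 as the total number of teeth.

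**5. Expected failures.** The 90% event probability implies 162 × 0.90 = about 146 events. If the event is major failure, 95% success implies 162 × 0.05 = 8.1.

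**6. Precision of the HR with 8.1 failures.** SE(log HR) = 2/√8.1 = 0.703. Around HR = 1, the 95% CI is exp(±1.96 × 0.703) = 0.25 to 3.96. The 90% CI is about 0.32 to 3.17.

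For a 90% CI centred on HR = 1 just to fit inside a symmetric margin, d must reach (2 × 1.64/|log margin|)²: about 85 events for HR 0.7, 969 for HR 0.9, 22 for log-HR 0.7 and 13 for log-HR 0.9. With about 8, TOST power is zero for all four. With the converted bound 3.17 and its reciprocal the interval only just fits, so power is still about 0.

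**7. Precision of the difference in success with the same data.** SE = √(2 × 0.95 × 0.05/81) = 0.0342. The 90% CI half-width is 1.645 × 0.0342 = 5.6 points. Power to lie within ±10 points is 2Φ(0.10/0.0342 − 1.645) − 1 = 80%. The article's 90% is the power for one side only.

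**The case against.** The article does mention an HR-scale TOST, so it presents the trial as powered on that scale too. The 10-point margin can also be converted to an HR once a control rate is assumed. A reader might infer that the planned HR cannot be tested against any equivalence hypothesis; that is too absolute. What can be said is that no single HR margin is fixed and that the range given conflicts with the 10 points.

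Other stronger readings also go beyond the text:

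- **A 5- to 19-fold gap between the margins.** This holds only if 0.7 to 0.9 are HRs (10/2.1 and 10/0.5). As log-HRs, the reading that comes closest to the stated power, the gap is about 1.5- to 2-fold (10/6.9 and 10/4.8).
- **An HR interval that could never exclude 1.43.** This is right for clearing both limits of 0.7 to 1.43, not for the upper limit alone. Likewise, the 90% upper limit would fall below 3.17 about half the time.
- **The 6-month result could be taken as decisive.** The objectives set a 2-year follow-up and no interim analysis is planned. The sentence listing four visits is loosely worded, no more.
- **Intention-to-treat as the only analysis set is a defect.** A per-protocol set may be in an analysis plan that is not shown, and the article does not describe replacing a lost ZC with an SSC.
- **The criterion would be chosen after seeing the data.** This is conjecture. A rule may exist elsewhere, and the statistician is to be blinded.

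The 90% event probability might also refer to success, which the model description codes as the dependent variable. The HR would then not be a failure HR, and the margin would still need to be stated.

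The mismatch of scales and the incompatible margins remain. Both are in the article's own text, so they are not detail left to another document.

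**Conclusion.** The concern holds in this form: the primary HR has no single pre-specified equivalence margin, the margin behind N = 81 is on another scale, and the range 0.7 to 0.9 agrees with it on neither reading. At the planning values (95% success, no true difference, 162 teeth), the sized criterion has about 80% two-sided power and the HR criteria have essentially none. Data that meet the 10-point criterion would therefore almost never show equivalence on the scale named for analysis.

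These figures rest on proportional hazards, independent teeth and about 8 failures. A higher failure rate would narrow the HR interval. The events needed for 80% power are far from 8 under most readings: about 268 for HR 0.7, 3,076 for HR 0.9 and 70 for log-HR 0.7. This should be settled before the data are analysed.

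**What to change.** Make the decisive equivalence test the within-child difference, ZC minus SSC, in the proportion free of major failure at 24 months. Use a matched-pairs 90% CI (a Tango score interval, for example), which agrees with the TOST Z of 1.64, and declare equivalence only if it lies within ±10 points. State how incomplete pairs are handled. Keep the adjusted frailty Cox HR and the 6-, 12- and 18-month results as supportive, and a per-protocol analysis as a sensitivity check rather than a second condition. Withdraw or correct the HR power statement.

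This keeps the sponsor's own margin and the planned 101 children, which already allow for 20% dropout. It costs revised wording and one small analysis. The drawbacks are that the covariate-adjusted HR is no longer the headline result, and that teeth censored before 24 months, which a Cox model uses directly, need a missing-data rule.

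The alternative is to fix and justify one HR margin and recompute power from the expected failures. With about 8 failures that is not workable for any margin in the stated range.

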### Study outcomes

The primary outcome is the success of the treatment. Success will be defined by the absence of major failure. A composite measure of signs and symptoms leading to diagnosis of irreversible pulpitis or periradicular periodontitis will be used to define major failure. This composite measure includes one or more of the following: pain, pulp infection, dental abscess, and periradicular pathology visible on radiograph [3].

The secondary outcomes are parental and child satisfaction (size, form, and color), retention and fracture of the PPC (two dichotomized variables, yes/no), the gingival state near the PPC using the indices Löe and Silness to record plaque index (PI), gingival index (GI) and depth of the pocket (DI) on the crowned tooth and the two adjacent teeth [8].

Parental and child satisfaction will be evaluated on a five-point Likert scale [11]. The DI will be assessed by soft periodontal probing on the sulcus mesial, distal, vestibular and lingual areas of the teeth. Finally, the wear of the antagonist tooth will be recorded (0: absence of wear; 1: wear on only the cusp point; and 2: wear at least at the cusps) [9, 10]. The presence or absence of a restoration with a dental material of the antagonist tooth will be also recorded.

Primary and secondary outcomes will be assessed clinically and radiographically by independent evaluators, one per center, at different periods during the study (postintervention and every 6 months during a total follow-up of 2 years). To prevent information bias, the evaluators will not be the operators who applied the treatment.

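### Retention and fracture happen once per crown but are assigned to a repeated-visit mixed model, which does not estimate the 24-month share of crowns that fail

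*Protocol article*

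**What the plan says.** Under Study outcomes, the protocol article defines "retention and fracture of the PPC (two dichotomized variables, yes/no" and schedules assessment "at different periods during the study (postintervention and every 6 months during a total follow-up of 2 years". The Statistical analysis section then announces: "Secondary analysis will be performed to compare: the secondary outcomes of retention and fracture of PPCs". The same list holds the plaque index, gingival index, pocket depth and antagonist wear. On timing it says: "Both the ITT and secondary analyses will be performed within a 2-year period at 6, 12, 18, and 24 months". On method it says: "Repeated measures analysis (mixed model approaches) will be performed, and the principal independent variables will be treatment and time". No other method is given for retention or fracture.

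The Cox model with shared frailty is described only for the primary outcome, absence of major failure. It is in those Cox sentences that "a random statement will be included identifying the variable “subject” as the variable that represents the clusters". For the mixed model the article states no cluster variable, link or covariance structure. It also does not say how a crown is scored at visits after it has been lost, broken, recemented or replaced.

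**The concern.** Plaque, gingival and pocket measures can rise and fall between visits, so a repeated-measures model with treatment and time suits them. Loss of retention and fracture are different: the question is whether a crown has failed by 24 months, and the first failure occurs once. A model of repeated statuses answers another question, and its answer depends on when failures occur and how later visits are scored.

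This matters because major failure is a pulpal and periradicular composite with no crown-level event. Retention and fracture are therefore the planned outcomes that show whether the crown itself holds. The Background explains that inner grooves are meant to improve retention and absorb stresses. The Discussion counts retention and integrity as part of a successful restoration.

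**Working it through.** **Inputs.** From the article: 81 teeth per group, one of each crown per child; follow-up visits at 6, 12, 18 and 24 months; alpha 5%. The article gives no event rate, margin or power for retention or fracture, so the rates below are assumptions.

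**1. The plan's own figure.** The 81 belongs to the primary outcome and reproduces: (1.645 + 1.282)² × [0.95×0.05 + 0.95×0.05] / 0.10² = 81.36. It is used here only as the number of pairs.

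**2. Records per event if status persists.** An event first seen at visit k (k = 1 to 4) is positive at 5 − k visits. Month 6 gives 4 records, month 12 gives 3, month 18 gives 2 and month 24 gives 1.

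**3. What the treatment effect then estimates.** Assume a constant event probability per visit and a 24-month risk p. Prevalence at visit k is 1 − (1 − p)^(k/4).

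| 24-month risk | Month 6 | Month 12 | Month 18 | Month 24 | Mean over visits |
|---|---|---|---|---|---|
| 5% | 1.27% | 2.53% | 3.77% | 5.00% | 3.14% |
| 15% | 3.98% | 7.80% | 11.48% | 15.00% | 9.57% |

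The visit-averaged contrast is 9.57 − 3.14 = 6.4 points. The 24-month risk difference is 15 − 5 = 10.0 points.

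**4. Simulation, unequal risks.** 81 pairs, persistent status, 4,000 replicates, child frailty SD 0 or 1 on the logit scale, two-sided 5%. The repeated analysis compares visit-averaged status within child with a variance that respects the tooth. The once-per-crown analysis compares 24-month status within child.

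| Assumed risks | Repeated contrast | Once-per-crown contrast | Power, repeated | Power, once per crown |
|---|---|---|---|---|
| 5% v 15% | 6.4-6.6 points | 10.0 points | 51-56% | 57-60% |
| 10% v 25% | 9.7-10.4 points | 14.8-15.1 points | 65-73% | 73-80% |

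**5. Simulation, equal risks of 5%, 10% or 20%.** The mean treatment difference is zero to within 0.1 percentage points for the repeated analysis. Type I error depends on the variance structure:

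- Once per crown, paired: 4.0-5.1%.
- Repeated statuses, tooth-level or child-robust variance: 4.1-5.1%.
- Repeated statuses, child random intercept only: 33-35% with a linear model; 34-38% with a logistic model (300 replicates, risks 10% and 20%).

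A further logistic check with a child intercept only, events spread evenly over the four visits and risks of 5-15%, gave 30-40%.

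**6. If status resets after repair.** The same child-intercept logistic model at 10% incidence rejects in about 3% of null runs. The estimate, however, moves with the scoring. Take 8 ZC fractures first seen at month 24 and 2 SSC fractures first seen at month 6. Persistent scoring gives 8×1 = 8 and 2×4 = 8 positive records, and an odds ratio of 1.00 (95% CI 0.31-3.19). Reset scoring gives 8 and 2 records, and an odds ratio of 4.13 (0.87-19.7). Cumulative incidence is 8/81 = 9.9% against 2/81 = 2.5% under either scoring.

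**The case against.** The strongest reply is that the severe consequences rest on choices the article does not make, and much of this stands.

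- **Error rate.** A reader might infer that the child is the only cluster in the mixed model and that the nominal 5% test is therefore badly wrong. The text does not support this: the subject cluster is named in the Cox sentences only. Covariance structure and link are details an article may leave to the full plan, so their absence is no finding. A logistic tooth-level intercept can be unstable for a status that never reverts, but the plan names no link.
- **Scoring.** Carrying a failure forward is a possible reading, not a stated rule. That is why both scorings are shown.
- **The 8-versus-2 example.** Its timing is extreme, and an exact McNemar test on it is also non-significant: if all ten pairs are discordant, p = 2×(1 + 10 + 45)/1024 = 112/1024 = 0.11. It illustrates dependence on scoring and nothing more.
- **A month-24 comparison may already be intended.** The sentence on analysis times can be read as one comparison per visit, and a treatment-by-time term is not excluded. Under persistent scoring that would recover much of what is needed. The article does not say so, however, and under reset scoring even month-24 status is not cumulative incidence.
- **Wider readings.** One might extend the point to major failure, because the timing sentence mentions the ITT analysis, or to antagonist wear. Major failure is explicitly given a Cox model. Dilution of a wear effect would require assuming steadily growing wear and no interaction term, neither of which is stated.

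What the reply does not remove is the choice of target. A suitable variance corrects the error rate but leaves the contrast as visit-averaged prevalence.

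**Conclusion.** The point holds in limited form. The article assigns two once-per-crown outcomes to a model suited to reversible measurements, and reserves first-event analysis for major failure. If status persists, the estimate is prevalence averaged over visits: about 6.5 instead of 10.0 points at assumed risks of 5% and 15%, with a modest loss of power (51-56% against 57-60%). If status resets, the result depends on how repaired crowns are scored. The estimate is not biased when the crowns are equal; it answers a different question from the share of crowns that failed.

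Inflated type I error, about 30-40%, is conditional on both persistent status and a child-only random effect. It is a risk to exclude, not an established defect. All these sizes rest on assumed event rates and, for the contrast and power, a constant event probability per visit. The outcomes are secondary, with no stated power or margin.

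**What to change.** In the Statistical analysis section:

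1. Analyse loss of retention and fracture as first events. Each crown counts once, at the visit where the event is first recorded, whatever its status at later visits.
2. Report the within-child ZC minus SSC difference in 24-month cumulative incidence with a paired 95% confidence interval.
3. Add time to first event, clustered by child, so that children lost before month 24 contribute. The shared-frailty Cox model already planned for the primary outcome serves for this.
4. Limit the repeated-measures mixed model, as far as this point goes, to the plaque index, gingival index and pocket depth.

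The cost is wording only: visits and collected data are unchanged. The small downside is that the 24-month paired summary ignores event timing, which the time-to-event analysis covers.

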### Data monitoring, harm, and auditing

The various centers will send their data to the coordinating center and data will be entered by the coordinating center. The data will be monitored by an independent clinical research assistant ([name]; Clinical Research Direction, CHUN).

No interim analysis is planned. Serious and nonserious adverse events will be assessed during the study by the evaluators. Trial management may be audited by the French Department of Health at any time; the audit would be independent of the investigators and sponsor. Investigators will not have access to the final trial dataset, which will be assessed by the blinded epidemiologist [name] following the recommendations of the statistician.

### Ethical consideration

The Clermont-Ferrand Committee of Protection of the People (CPP; Sud-Est VI) has approved the study protocol in February 2018 (2017-A01952–51). The protocol is registered with the IDRCB (2017-A01952–51) at the French National Agency for Medicines and Health product Safety (ANSM) and in Clinicaltrials.gov (NCT03296709). All amendments to the protocol will be justified and submitted to the scientific board, accepted by the CPP, and recorded by the ANSM. Changes and amendments will be also recorded at ClinicalTrials.gov. Informed consent will be obtained from each eligible child and their legal guardians after an explanation of the trial by an investigator of the corresponding center. Patients and legal guardians are informed that they have the right to withdraw from the study at any time and without giving reasons. Regardless of withdrawal, patients will be provided with any necessary treatment in their best interest. Withdrawal will be documented. Data confidentiality was audited by the National Committee of Informatics and Freedom (CNIL; reference methodology 001). First and last names of included patients are not recorded in the database. Neither additional visits nor complementary examinations are needed compared with the conventional caries management for children at high risk of caries (our target population). However, the consultation may take a little longer because of the indicators used and the data collection. These methods of monitoring due to the research requirements involve only negligible constraints.

